#### Monitoring and Iterative Improvement

The monitoring and evaluation process will be conducted on users and health care providers. This study uses a mixed method, pre-post implementation design to evaluate the introduction and scale-up of the e-SAATHI MH chatbot in Assam. While this design enables comprehensive assessment of both quantitative outcomes and qualitative experiences, we acknowledge that the absence of randomization limits the strength of causal inference. To address potential sources of bias, we will implement several strategies, including adjustment for district-level clustering, accounting for secular trends over time, and controlling for measured confounders in the analysis. These approaches aim to strengthen the validity of our findings and provide a nuanced understanding of the intervention’s impact in real-world settings.

All the developed data collection instruments and procedures will be pretested in settings like those in which they will be administered. Guidance will be sought from postnatal women who have recently given birth when finalizing the instruments to ensure that questions and the data collection procedures are conducted with appropriate sensitivity and are not perceived as stigmatizing. The study tools will be pretested among a small group of women with characteristics similar to those of the study population to identify potential negative consequences and will be modified accordingly. Study tools for postnatal women will be translated and pretested in Assamese and Hindi.

The study comprises 5 main data collection tools that are described in Table 1: (1) in-depth qualitative interviews with MH providers; (2) in-depth qualitative interviews with postnatal women; (3) telephone interviews with postnatal women and MH chatbot users; (4) health facility inventory; and (5) MH digital platform program data.

**Table 1. T1:** Data collection activities.^a^

	1. IDIs^b^ with health care providers	2. IDIs with postnatal (PN^c^) women	3. Survey with PN women	4. Facility inventory and routine data	5. MH^d^ data from chatbot platform
Study population	Purposively selected providers from various care levels (public and private)	Purposively sampled PN women using chatbot <6 mo since childbirth	PN women recently given birth in last 2‐8 wk	Facility providing MH services	Pregnant and PN women onboarded to chatbot (deidentified)

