#### Quantitative Analysis

Raw quantitative data collected from the postnatal women’s survey (dipstick survey) will be cleaned and checked for errors and outliers. Data cleaning and quality checks will occur fortnightly during collection with a comprehensive pass before midline and endline analyses. Descriptive statistics (means, SDs, medians, and frequencies) will summarize baseline characteristics and outcomes. The primary outcome, the composite quality score of maternal and newborn care [24] and secondary outcomes (service uptake indicators, user-reported knowledge and self-care practices, and satisfaction with care) will be compared between baseline and follow-up.

Normality will be tested (Shapiro-Wilk). Parametric (*t* tests, ANOVA) or nonparametric (Wilcoxon and Mann-Whitney) tests will be used as appropriate. Categorical variables will be analyzed using chi-square or Fisher exact test. Multivariable analyses will use generalized linear/logistic mixed models to adjust for clustering (facility/district) and confounders (age, parity, socioeconomic status, dose of exposure-engagement frequency, and enrollment channel). For repeated measures, mixed-effects models will assess changes over time. Multiple comparisons will be adjusted using Bonferroni or FDR. All analyses will be performed in IBM SPSS Statistics (Version 29.0; IBM Corp) and R Core Team. Results will be visualized with tables and graphs. Statistical significance is set at *P*<.05, with effect sizes and 95% CIs reported.

Interim analyses will be conducted after midline data (Phase 2) collection completion in 2026; final analyses will be performed after endline data collection in 2027.

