### Addressing Digital Inclusion and Equity

Despite the promise of digital health solutions, challenges related to equity and inclusion must be addressed. Vulnerable subgroups, such as women with low literacy levels or those residing in remote areas without smartphones, may face barriers in accessing e-SAATHI’s services. These concerns are explicitly addressed in the intervention’s design. The chatbot platform is delivered via widely available messaging apps such as WhatsApp, ensuring accessibility for diverse user groups. Content is provided in local languages, including Assamese and Hindi, to maximize comprehension and cultural relevance. Collaborations with ASHAs and nurses further enhance trust and engagement among users. This blended approach mirrors the successful integration of digital and human-mediated services observed in South Africa’s MomConnect initiative [31,32].

Infrastructure obstacles, such as poor connectivity in rural areas, are mitigated through asynchronous messaging capabilities, allowing users to access content even in regions with intermittent internet access. By prioritizing inclusive design features, e-SAATHI ensures its accessibility to underserved populations, thereby enhancing its scalability and impact.

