#### Limitations

The implementation of the e-SAATHI intervention faces several limitations. First, digital access barriers remain a concern, as users in areas with limited or no internet connectivity may be unable to access the chatbot. Some pregnant and postnatal women may not have smartphones or internet access, potentially excluding those who most need information. Although mobile phone density is generally adequate in the study districts, alternative delivery mechanisms—such as dissemination through ASHAs or other media—are being explored to address this gap. Additionally, systemic and operational challenges could arise, as the alignment of partner facilities and district health officials with the intervention’s goals may vary, potentially causing delays. Microplanning differences in implementation could also result in varied onboarding and user experiences across sites. The study design presents another constraint; while the pre-post monitoring and evaluation framework is practical for real-world application, it limits the strength of causal inferences. Without randomization, observed changes may be influenced by external factors or secular trends, despite efforts to adjust for confounders and clustering. There is also the potential for selection bias, as women who are able to access and use the chatbot may differ systematically from those who cannot, which could affect the generalizability of the findings.

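### The listed confounders leave out literacy, smartphone access and rural residence, which the article itself names as barriers to chatbot access

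*Protocol article*

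**What the plan says.** The primary outcome is the composite quality score, compared between baseline and follow-up. For the multivariable analysis, the Quantitative Analysis section plans "generalized linear/logistic mixed models to adjust for clustering (facility/district" and then names "confounders (age, parity, socioeconomic status, dose of exposure-engagement frequency, and enrollment channel". The list is written as complete, with no sign that its items are examples.

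The Monitoring and Iterative Improvement section acknowledges that the design is not randomized. Its remedies for bias are adjustment for district clustering, allowance for secular trends, and "controlling for measured confounders in the analysis".

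The Discussion says who is less able to reach the chatbot. Under Addressing Digital Inclusion and Equity: "women with low literacy levels or those residing in remote areas without smartphones, may face barriers in accessing" the service. Under Limitations: "Some pregnant and postnatal women may not have smartphones or internet access, potentially excluding those who most need information". The same section adds that "women who are able to access and use the chatbot may differ systematically from those who cannot, which could affect the generalizability of the findings".

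The article describes the survey sample in two ways. The Population section says that chatbot users take part in the quantitative dipstick surveys. The description of the survey under Monitoring and Iterative Improvement takes in women on the postnatal ward who have been through pregnancy and childbirth, used the chatbot, or both.

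**The concern.** In a pre-post comparison without randomization, the covariates must carry whatever differs between the women surveyed at baseline and those surveyed later. The article names three factors that govern access to the chatbot, and all three plausibly also affect antenatal and postnatal care. None is on the list by name.

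The list is also shorter than it looks. Engagement dose and enrollment channel are defined only for women who joined the chatbot. They describe exposure and cannot balance baseline against follow-up. That leaves age, parity and a socioeconomic status that the article does not define.

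At stake is whether a higher score at follow-up reflects the chatbot or a follow-up sample with more education, more smartphones or easier access to care. That is bias in the effect estimate. The Limitations section ties the selection of users only to generalizability.

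**Working it through.** **1. Text check.** The article states no figure on this point to reproduce, so the first step sets the barriers beside the model terms.

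| Barrier named in the Discussion | Listed by name? | Possible partial cover |
|---|---|---|
| Low literacy | No | Socioeconomic status, if it includes education |
| No smartphone or internet | No | Socioeconomic status, if it includes phone ownership |
| Remote residence | No | Facility/district terms |

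None of the three is listed, and each has at best a proxy. The facility/district terms serve mainly to handle correlation. They cannot fully remove differences that come from sites with no baseline data, which could arise if survey sites follow the rollout from 5 facilities to 3 and then 10 districts.

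**2. When it bites.** It depends on who is surveyed.
- If follow-up respondents are chatbot users (Population section), all of them can use WhatsApp, because subscription runs through it (Chatbot section). If baseline women were not chosen on access, the mix differs between waves.
- If every wave samples all ward women, selection into chatbot use does not by itself bias the wave contrast. A change in smartphone access over the years of data collection (November 2023 to 2027) still could, but that such a change occurs is an assumption.

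**3. Illustration of size, smartphone access only.** Bias = (follow-up share − baseline share) × score gap between women with and without access × (1 − share absorbed by socioeconomic status and cluster terms).

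Inputs:
- Baseline share 0.26: smartphone ownership among women in India, from the Introduction. It is not a figure for these wards.
- Follow-up share 0.50 to 1.00, gap 0.1 to 0.5 SD, absorbed share 0 to 0.5: all assumed.
- 200 women per wave: Table 1 gives 200, and per wave is assumed. Clustering is ignored.

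SE of the difference = √(2/200) = 0.10 SD. Detectable difference at 80% power (assumed), two-sided 0.05 = (1.96 + 0.84) × 0.10 = 0.28 SD. False-positive rate = Φ(−1.96 + bias/0.10) + Φ(−1.96 − bias/0.10).

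| Follow-up share | Gap (SD) | Absorbed | Bias (SD) | False-positive rate |
|---|---|---|---|---|
| 0.26 | any | any | 0 | 5.0% |
| 0.50 | 0.1 | 0.5 | 0.24 × 0.1 × 0.5 = 0.012 | 5.2% |
| 0.50 | 0.2 | 0 | 0.24 × 0.2 = 0.048 | 7.7% |
| 1.00 | 0.2 | 0.5 | 0.74 × 0.2 × 0.5 = 0.074 | 11.5% |
| 1.00 | 0.2 | 0 | 0.74 × 0.2 = 0.148 | 31.6% |
| 1.00 | 0.5 | 0 | 0.74 × 0.5 = 0.370 | 95.9% |

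The range shows that the omission can matter or can be negligible. It does not estimate the bias in this study.

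**The case against.** The strongest reply is that the article does not hide the problem. It promises control of measured confounders only, and its Limitations section concedes that external factors and secular trends may remain despite adjustment. A reader might infer that the plan claims to control selection into chatbot use and then misses its main drivers. The documents support neither half. No section says that selection is controlled, and the Discussion lists barriers without ranking them.

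Further points on that side:
- Socioeconomic status may include education or phone ownership, and how it is built is a detail an article can leave to the full protocol. This stands, and it is why the proxies count as partial cover.
- No user versus non-user comparison is specified; the planned contrast is baseline versus follow-up. This stands, so the point is confined to that contrast.
- Rising smartphone access is a secular trend, which the plan says it will account for. This stands only in part: no concurrent comparison group is described, so an access trend cannot be separated from wave unless access is measured.
- An item not asked at baseline cannot adjust the baseline contrast. This stands and limits the fix.
- Smartphone access is a precondition for receiving the chatbot, so adjusting for it could remove some programme effect if wider access raises outcomes through chatbot reach. This is a reason to show both estimates.

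The baseline's own status is also not fully clear. Table 1 sets follow-up nine months after chatbot introduction, but the Results section dates chatbot data from April 2023 and evaluation data from November 2023. The argument therefore stays conditional on how baseline women were chosen.

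**Conclusion.** The point holds as a gap in the stated adjustment set. The list omits education or literacy, smartphone access and rural or remote residence, which the article itself names as access barriers. Socioeconomic status and the cluster terms cover them only partly, and two of the five listed items cannot act as confounders of a baseline versus follow-up contrast. If the mix of these factors differs between waves, the adjusted difference is biased. That is likely if follow-up respondents are chatbot users and less so if every wave samples all ward women.

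The size cannot be derived from the documents. The 0.01 to 0.37 SD range for unequal mixes rests on assumed shares, gaps and absorption, on a national ownership figure and on 200 women per wave. With an equal mix the bias from this factor is zero. It would be wrong to read the range as showing that the primary result will be false.

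**What to change.** - Add education or literacy, own or household smartphone access, and rural/urban residence to the adjustment set of the baseline versus follow-up models wherever they were collected at baseline.
- Ask all three in every remaining wave.
- Report estimates with and without them.
- Where an item is missing at baseline, use it only for comparisons among later waves or within a wave, and state that the baseline contrast is not adjusted for it.
- Reconcile the Population section with the survey description under Monitoring and Iterative Improvement on who is surveyed at each wave.
- In Limitations, say that differences in access between compared groups can bias the effect estimate as well as limit generalizability.

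The cost is a few short survey items and slightly larger models. The main downside is that some items may be absent from the baseline wave, in which case the primary contrast stays unadjusted for them. The change is best settled before the midline analysis in 2026.

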#### Data Confidentiality

Any personal, organizational, or identifier information will not be attached to the data, nor will it be linked to the reports in a way that is traceable to an individual. Specifically, no names will be included in the transcripts, facility, and village names (that may characterize a community) will be described vaguely as a “rural” or “peri-urban site.” Pseudonyms or numbers will be assigned in naming stored data files to protect respondents from being identified. During dissemination of any type, all data will be presented in aggregate form so that names and other identifying information of a respondent will not be exposed—for example, an IDI with a postnatal woman will be classified in these ambiguous terms. Similarly, an IDI with a health provider will be described without explicitly naming a facility or area in which the data was collected. All data will be collected under the regulation of the data protection and management guidelines provided by the Government of India.

### Ethical Considerations

The research protocol has been reviewed by key stakeholders and ethical clearance has been granted by the Population Council’s Institutional Review Board (517), and the SBISR Ethics Committee (F.2/SBISR-EC/PR 01‐23). All researchers and research assistants will be trained on the conduct of ethical procedures and will be monitored during field work by the coalition led by PPC/SBISR. Informed consent will be obtained separately for each study participant and each component. All participants will be given detailed information about the study, including aims and methods of study; institutional affiliations of the research; anticipated benefits, risks, and discomfort it may cause (expected to be minimal); follow-up of the study; expected duration of an interview; a participant’s choice not to answer any questions; that they have the right to abstain from participating in the study or to withdraw from it at any time, without reprisal; measures taken to ensure confidentiality and anonymity of information provided; the conduct of interviews in places chosen by a participant that may maximize audio privacy; and contact details of the study coordinator for any questions or concerns. All data will be stored in password-protected computer files. Hard copies of questionnaires and anonymized transcriptions will be stored securely in a locked cabinet, in accordance with the PCC and SBISR policy. No compensation will be provided to participants.

## Results

The e-SAATHI study was formally funded in September 2022, marking the commencement of project activities. Since the initiation of the program, significant progress has been achieved in both the onboarding of health care facilities and participant recruitment. As of December 2025, a total of 210 health facilities across Assam have been successfully integrated into the e-SAATHI network. A total of 201,813 women have been enrolled to receive MH support through the chatbot platform.

Chatbot-based data collection was launched in April 2023 and is scheduled to continue through June 2027, ensuring comprehensive coverage of the intervention period. The collection of qualitative and quantitative evaluation data began in November 2023, providing a robust foundation for assessing both user experiences and measurable outcomes.

Interim analyses are planned following the completion of midline data collection in 2026, which will offer early insights into the effectiveness and operational feasibility of the intervention. Final analyses are scheduled to take place after endline data collection in 2027, at which point the full impact of the e-SAATHI program will be evaluated and published. The primary outcome of interest is the change in the composite quality score of maternal and newborn care, serving as a key indicator of the intervention’s effectiveness. Secondary outcomes include a range of service uptake indicators, user-reported knowledge and self-care practices, and satisfaction with care received. The study will also assess operational feasibility, including the integration of providers into the digital system and the identification of barriers such as digital literacy and connectivity challenges.

As of the writing of this paper (December 2025), we are completing phase 2 and initiating in-depth impact evaluation.

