**Methods:**

Phase 1 (0‐3 mo) involves co-designing and pilot testing aligned with World Health Organization and national guidelines. Phase 2 (4‐24 mo) involves enrolling pregnant and postpartum women via health facilities and social media. The chatbot sends 2-3 messages weekly from 10-week pregnancy to 15 weeks postpartum. About 300 health care providers will be trained and engaged for onboarding and feedback. Phase 3 (25‐36 mo) involves scaling up across districts, reaching 225,000 women. Data collection includes interviews, surveys, facility assessments, and chatbot analytics. Qualitative analysis will explore experiences; quantitative data (ANC completion, facility delivery, PNC follow-up, and satisfaction) will compare pre- and post-interventions. Ethical approvals, informed consent, and data confidentiality are observed.

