### Phase 2: Engagement, Monitoring, and Iterative Improvement (April 2023-September 2025)

#### Engagement

Onboarded women will be regularly engaged by health care providers or the research team whenever visiting the health facility to identify any challenges they face while using the chatbot. Additionally, feedback will be collected from users regarding the quality and usefulness of the services provided by the e-SAATHI chatbot.

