Sample size	10 from range of facility levels periodically	2‐4 women per facility—periodically	200 PN women	Each facility taking part in the project	All women who use chatbot
Location of activity	Private room at health facility or mutually agreed site	Private room at health facility or mutually agreed site	Recruitment at PNC^e^ ward then short interview (2‐8 wk later)	Facility level data (deidentified)	Online program data
Timing	Baseline and periodically 6‐9 mo	Baseline, midline, and endline	Baseline, then periodically (9 mo after chatbot introduction)	Quarterly	From initiation of chatbot to end of project
Method	In-depth face-to-face interview by researcher	In-depth face-to-face interview by researcher	Short in-person/telephone survey by researcher	Facilities visited by researcher	Analysis of chatbot program data

a Analysis of baseline, midline, and endline data will occur after the completion of each respective phase; interim analyses will be performed after midline (2026) and final analyses after endline (2027).

b IDI: in-depth interview.

c PN: postnatal.

d MH: maternal health.

e PNC: postnatal care.

First, this includes any MH provider (at least 10) over 18 years, who consent to be interviewed and work in one of the public or private facilities in the study areas, nurses, midwives, auxiliary nurse midwives, Accredited Social Health Activists (ASHAs), and doctors at health facilities engaged in the digital MH support system. The purpose of the interviews with MH providers is to identify facility and provider-specific issues that may affect the delivery of care and uptake of women onboarding onto the chatbot. Researchers will use a short in-depth interview (IDI) guide to ask respondents about their expectations regarding the MH chatbot, its strengths and weaknesses, develop an in-depth understanding of the process of introducing the chatbot, and how it might be improved and subsequently scaled up. Data will be analyzed iteratively after each collection wave to inform ongoing implementation and comprehensively the completion of phase 2.

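### Evaluation data start about seven months after the chatbot went live, so a baseline defined by survey wave may include women already exposed to it

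*Protocol article*

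**What the plan says.** **Launch.** The Results section states "Chatbot-based data collection was launched in April 2023 and is scheduled to continue through June 2027". Table 1 gives the span of the chatbot platform data as "From initiation of chatbot to end of project", so April 2023 is the date the chatbot went live. The same month opens the section headed "Phase 2: Engagement, Monitoring, and Iterative Improvement (April 2023-September 2025", and the Abstract says this phase "involves enrolling pregnant and postpartum women via health facilities and social media".

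**Evaluation.** The Results section then says "The collection of qualitative and quantitative evaluation data began in November 2023". The Abstract gives the same month.

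**Comparison.** The section Monitoring and Iterative Improvement describes a pre-post design without randomization. Under Quantitative Analysis, the primary composite quality score and the secondary outcomes "will be compared between baseline and follow-up". Table 1 times the postnatal survey as "Baseline, then periodically (9 mo after chatbot introduction" and gives a sample of 200 women.

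**Who is surveyed.** The survey description takes postnatal women whether or not they used askNivi, interviews them two to eight weeks after delivery, and asks about their experience of the chatbot. The Population section says that chatbot users take part in these surveys. The Chatbot section runs messages from week 10 of pregnancy to week 15 after birth and lets women join through a social media advertisement as well as at a facility.

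**Roll-out.** It is staggered: 5 facilities, then 3 districts, then 10 districts.

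**The concern.** The pre-post contrast is the only quantitative effectiveness comparison in the article. Each survey interview is a single contact, so no woman supplies her own pre-exposure value. The baseline wave alone stands in for what would have happened without the chatbot.

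On the stated dates, no survey baseline can precede November 2023, when the chatbot had been live for about seven months. Table 1 times follow-up from chatbot introduction, which reads as though baseline came before it. If some baseline women had used the chatbot, part of its effect already sits in the reference value, and the estimated change in the composite score and in ANC and PNC uptake shrinks. A null or small result could then not be told apart from a real effect measured against a contaminated baseline.

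**Working it through.** The article states no effect size, standard deviation or power, so there is no figure of its own to reproduce. The check is date arithmetic followed by a dilution formula.

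**Step 1: the gap.** From 1 April to 1 November 2023 is 214 days, that is 214/7 = 30.6 weeks or 7 months. The first of April is an assumption; the article gives only the month.

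**Step 2: possible exposure of November 2023 respondents.** Inputs are interview at 2 to 8 weeks after delivery, messages from week 10, and an assumed delivery at 40 weeks. The antenatal program then lasts 40 − 10 = 30 weeks.

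- Delivery date = interview date − 2 or 8 weeks.
- Gestation on 1 April = 40 − (weeks from 1 April to delivery).
- Maximum antenatal exposure = 40 − max(gestation on 1 April, 10).

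| Interview | Weeks since delivery | Delivery | Gestation on 1 April | Maximum exposure |
|---|---|---|---|---|
| 1 Nov | 2 | 18 Oct | 40 − 200/7 = 11.4 wk | 28.6 wk |
| 1 Nov | 8 | 6 Sep | 40 − 158/7 = 17.4 wk | 22.6 wk |
| 30 Nov | 2 | 16 Nov | 40 − 229/7 = 7.3 wk | 30.0 wk |
| 30 Nov | 8 | 5 Oct | 40 − 187/7 = 13.3 wk | 26.7 wk |

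The range is 22.6/30 = 75% to 100% of the antenatal program. These are maxima, for a woman who subscribed at the first opportunity. If November marks recruitment on the postnatal ward rather than the first interviews, deliveries fall in November or later. A woman delivering on 1 November was 40 − 30.6 = 9.4 weeks pregnant at launch, so all 30 weeks were open to her.

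**Step 3: dilution.** Let δ be the effect in exposed women, and f0 and f1 the exposed shares at baseline and follow-up. With no other change over time and the same δ in both waves, the expected difference is δ(f1 − f0). With a clean baseline it is δf1. The retained fraction is (f1 − f0)/f1.

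**Step 4: what this could mean.** The article gives neither share, so every value below is assumed: f1 = 1, a standardised effect of 0.30, 200 women per wave, two-sided alpha 0.05, no clustering.

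| f0 | Effect retained | Power | Women per wave for 80% power |
|---|---|---|---|
| 0 | 100% | 85% | 175 |
| 10% | 90% | 77% | 216 |
| 25% | 75% | 61% | 311 |
| 50% | 50% | 32% | 698 |

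At the benign end, f0 = 5% with f1 = 60% retains (0.60 − 0.05)/0.60 = 92%.

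**Step 5: does the planned adjustment repair it?** The mixed models list dose of exposure among the confounders. Dose is the intervention itself. Conditioning on it leaves the wave coefficient as the change not explained by chatbot use. It does not recreate an unexposed baseline.

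**The case against.** The strongest reply is the staggered roll-out. With 5 facilities at the start, a November 2023 survey could be a true pre-period at sites the chatbot had not reached, and the exposed share could be low. A condensed article need not list survey sites by wave. This stands: contamination is possible but not demonstrated. It does not dispose of the point, because the analysis is fixed by wave label, users are admitted to the survey, and social media sign-up reaches women outside onboarded facilities.

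Two inferential steps should also be granted. No sentence gives the date of first enrolment; April 2023 follows from the launch and the Phase 2 dates. Nor is the November collection called baseline; it is simply the earliest evaluation collection.

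A reader might infer more than the documents support:

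- *That follow-up was due in January 2024, two months after baseline.* This counts Table 1's nine months from one statewide date, whereas introduction is staggered. The article also places the midline analysis in 2026 and the final analysis in 2027.
- *That the result is biased toward no effect overall.* Contamination alone pulls that way. The secular trends and selection that the article acknowledges could push the other way, so the net direction is not established.
- *That the step 2 figures measure dilution.* They bound one woman's exposure and say nothing about how many surveyed women subscribed.

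It is fair to add that the survey already asks about askNivi use, so exposure can be classified at analysis. The Limitations section covers secular trends, selection and access, but not exposure at baseline.

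**Conclusion.** The point holds in conditional form. Evaluation data began about seven months after launch, and a comparison by wave label can count as unexposed women who had access to at least three quarters of the antenatal program. That rests on launch at the start of April 2023, enrolment from launch, and delivery at 40 weeks.

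The loss is the factor (f1 − f0)/f1. Because neither share is given, it may lie anywhere from negligible to serious, and no corrected effect or power can be derived. The remedy is a change of analysis definition. According to the Results section, Phase 2 was being completed and the impact evaluation begun in December 2025, so it can still be settled before the 2026 interim analysis.

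**What to change.** 1. Define the pre-period by facility and date: a woman is pre-intervention if she delivered before her facility's onboarding date. Analyse November 2023 respondents from facilities already onboarded as early-exposed, and state when and where each wave was taken relative to onboarding.
2. Report self-reported askNivi use in every wave. This also shows social media users at facilities not yet onboarded. Platform data are deidentified, so linkage to individual women may not be possible.
3. Exclude baseline users only as a sensitivity analysis. Removing them from one side of the comparison selects on uptake.
4. Take engagement dose out of the confounder set of the primary pre-post model. It can be examined separately as a dose-response question.
5. For ANC and PNC uptake, use facility monthly counts from before onboarding where they can be extracted. The article does not say how far back they reach, and they cannot supply the composite score.

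The cost is merging onboarding dates into the survey file, extracting earlier register months, and having fewer true baseline women. Facilities onboarded at launch may have none; their composite-score result should then not be called pre-post.
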